## Methods

### Study Design

The Predictive and Prognostic Biomarkers in Patients With MF and SS (BIO-MUSE) study is a translational prospective study, aiming to include 120 adult patients with MF and SS and a control group of 20 healthy volunteers (Figure 1). Sampling of each patient will be performed every 3 months for 3 years. The control group will be examined on 3 different occasions at least 2 months apart. This study is presently open at Skåne University Hospital and aims to open at Karolinska University Hospital. The multicenter study design enables other Swedish sites to be included, after further ethical approval.

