### Serum-Based Profiling of Immune-Related Soluble Proteins

Broad sets of serum-based protein profiling focused on immune-related proteins will be performed in patients. Global protein profiling will be performed using commercially available methods, allowing high-plex analyses of immune-related soluble molecules. State-of-the-art bioinformatic tools will be applied for preprocessing and analysis of data (Multimedia Appendix 1).

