### Statistical Analysis

The sample profiles from patients with an early stage of disease (stage IA-IIA) will be compared to samples from patients with an advanced stage of disease (stage IIB-IVB) using multivariate analysis with principal component analysis. Individual samples will be compared between the groups using the Mann-Whitney *U* test. Other translational samples will be presented by descriptive statistics. Progression-free and overall survival will be presented using Kaplan-Meier plots.

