## Results

Patient inclusion started in 2021 and is still ongoing in December 2023, with 18 patients and 20 healthy controls enrolled. Until December 2023, a total of 2 included patients have declined further participation due to the extra visits in this study. Further, 2 patients have died from MF during this study. The publication of selected translational findings before the publication of the main results of the trial is accepted, and data analysis is in progress.

The evaluation of the stage of the disease will be observed every 3 months according to the TNMB classification, where the shift from one stage to another implies progression or treatment response. After the study, patients will be grouped as either early stage of the disease (IA-IIA) or advanced stage of the disease (IIB-IVB). The patients crossing over from the early stage of the disease to the advanced stage of the disease group will be analyzed both individually and as a group. Approximately 30% (36/120) of patients are estimated to be in the advanced stage of the disease group. The translational samples in the early stage of the disease group will be compared to samples from the advanced stage of the disease group. The treatments directed against MF are documented throughout this study. Excluded patients will be presented along with the final results. Depending on patient numbers, treatment data will be presented descriptively, or if possible, to support data on treatment predictive biomarkers.

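### The early-versus-advanced comparison names Mann-Whitney on samples without fixing one value per patient; if the serial samples are pooled, a nominal 5% test could have a false-positive rate of about 19% to 52%

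*Protocol article*

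**What the plan says.** Statistical Analysis in the protocol article first compares sample profiles of early-stage (IA-IIA) and advanced-stage (IIB-IVB) patients by principal component analysis. It then states: "Individual samples will be compared between the groups using the Mann-Whitney" U test. The rest is descriptive statistics and Kaplan-Meier plots, so Mann-Whitney is the only test named.

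The sampling intensity is in Study Design: "Sampling of each patient will be performed every 3 months for 3 years".

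The Results section describes the groups and the comparison:

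- "After the study, patients will be grouped as either early stage of the disease (IA-IIA) or advanced stage of the disease (IIB-IVB").
- "The translational samples in the early stage of the disease group will be compared to samples from the advanced stage of the disease group".
- "Approximately 30% (36/120) of patients are estimated to be in the advanced stage of the disease group".
- "The patients crossing over from the early stage of the disease to the advanced stage of the disease group will be analyzed both individually" and also as a group. The text does not say on which side of the two-group test their samples fall.

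None of these sections names a visit, a per-patient summary or a method for repeated measurements.

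**The concern.** Both sentences on the comparison take the sample as the unit, while stage group is mainly a property of the patient. Repeated values of a protein or cell subset in one patient are likely to resemble each other. A test that treats them as separate observations counts the same patient several times and understates the variance of the group difference.

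If the plan were carried out that way, markers could be declared stage-associated because of repeated sampling alone. Patients with long follow-up would also weigh more than those who leave early. That is not hypothetical here: among the 18 patients enrolled, "a total of 2 included patients have declined further participation due to the extra visits in this study", and 2 others died. The matter is current, because the Results section allows selected translational findings to be published before the main results and says that analysis is under way.

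**Working it through.** **Inputs from the article**

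- Group sizes: 36/120 = 0.30, which reproduces the stated 30%; early stage is 120 − 36 = 84.
- Samples per patient, m: 36 months / 3 = 12, or 13 if a baseline sample is counted. This is a maximum.

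**Inputs assumed, because the article does not give them**

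- Two-sided level 0.05.
- Within-patient correlation (ICC) from 0.05 to 0.9.
- All serial samples pooled, with each patient in one group throughout.

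**Formula.** Design effect D = 1 + (m − 1) × ICC. Actual false-positive rate = 2 × [1 − Φ(1.96/√D)].

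Worked case, m = 13 and ICC = 0.3: D = 1 + 12 × 0.3 = 4.6; 1.96/√4.6 = 0.914; rate = 36%.

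| ICC | D (m = 13) | Rate, m = 13 | Rate, m = 12 | Rate, m = 6 | Rate, m = 3 |
|---|---|---|---|---|---|
| 0.05 | 1.6 | 12.1% | 11.5% | 8.0% | 6.2% |
| 0.1 | 2.2 | 18.6% | 17.6% | 11.0% | 7.4% |
| 0.3 | 4.6 | 36.1% | 34.5% | 21.5% | 12.1% |
| 0.5 | 7.0 | 45.9% | 44.2% | 29.5% | 16.6% |
| 0.7 | 9.4 | 52.3% | 50.6% | 35.6% | 20.6% |
| 0.9 | 11.8 | 56.8% | 55.3% | 40.3% | 24.1% |

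**Check by simulation.** The Mann-Whitney test was applied to simulated null data, 84 versus 36 patients, 3000 data sets per setting.

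- m = 13, constant correlation: 19%, 36%, 44% and 54% at ICC 0.1, 0.3, 0.5 and 0.7, close to the formula.
- m = 13, correlation decaying over time (AR(1)): 25%, 35% and 50% at rho 0.5, 0.7 and 0.9.
- Up to 13 samples with an assumed 5% dropout per visit: 32%, 45% and 50% at ICC 0.3, 0.5 and 0.7.
- 13 versus 5 patients, an assumed split of the 18 enrolled, 13 samples each: 36%, 45% and 53% at ICC 0.3, 0.5 and 0.7. The inflation does not shrink when there are fewer patients.

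**Check of the remedy.** With one value per patient, D = 1 and the formula gives 5%. Simulation with 10,000 data sets gave 4.8%; the simulation error is √(0.05 × 0.95/10,000) = 0.2 percentage points, so this agrees with the nominal level.

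**The case against.** The strongest objection is that pooling is only one reading. The sentence follows one on multivariate profiles, and the article often uses the word sample for a type of specimen or assay. Individual samples may therefore mean single analytes as opposed to the whole profile. If each analyte is then tested at one visit or on a per-patient summary, the test is valid at 5%. This stands, and it makes the inflation conditional. It does not settle the matter, because under that reading the article still does not say which of up to 12 or 13 visits supplies the value.

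It can also be said that a short statistics section leaves the handling of repeated samples to the full plan. That would hold if the article were silent. Instead it names a test and, twice, samples as what is compared.

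Two stronger conclusions are tempting, and the documents support neither:

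- A reader might infer that the false-positive rate is in fact 30% to 50%. The article gives neither the correlation nor the test level. That band needs an ICC of about 0.21 to 0.62 at m = 13, and the rate runs from 12% to 57% over ICC 0.05 to 0.9. The schedule for each assay is in Multimedia Appendix 1, which is not shown, and withdrawals and deaths lower m. Patients who change stage may contribute samples to both groups, which changes the size of the inflation.
- A reader might add a count of false markers, since the serum profiling is described as "allowing high-plex analyses of immune-related soluble molecules". No number of markers is stated, and control of multiplicity is commonly left to the analysis plan, so no such claim is made here.

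**Conclusion.** The point holds in conditional form. The article names an independence-based test for samples, schedules many samples per patient and does not fix one value per patient. Followed literally, with 13 pooled samples per patient, it would have a false-positive rate of about 19%, 36% and 52% at ICC 0.1, 0.3 and 0.7; at 3 samples per patient it would be about 12% to 21% at ICC 0.3 to 0.7. These figures rest on the assumed level, correlations and pooling, and on each patient staying in one group. What is established is that the unit of analysis is left open between a valid 5% test and a badly inflated one. That is worth correcting before any stage comparison is reported.

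**What to change.** State in Statistical Analysis that every Mann-Whitney comparison of early with advanced stage uses one value per patient, for example the inclusion sample, and state which stage assessment places the patient in a group for that value.

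For the serial samples, replace Mann-Whitney with a linear mixed model with a patient random intercept (on log- or rank-transformed values where needed), or a GEE with standard errors clustered on patient. Enter stage at sampling as a time-varying factor, so that patients who change stage contribute to both categories with their correlation accounted for.

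No additional patients or samples are needed. The cost is a change of wording, modest extra analysis work and, probably, fewer nominally significant markers.

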## Results

Patient inclusion started in 2021 and is still ongoing in December 2023, with 18 patients and 20 healthy controls enrolled. Until December 2023, a total of 2 included patients have declined further participation due to the extra visits in this study. Further, 2 patients have died from MF during this study. The publication of selected translational findings before the publication of the main results of the trial is accepted, and data analysis is in progress.

The evaluation of the stage of the disease will be observed every 3 months according to the TNMB classification, where the shift from one stage to another implies progression or treatment response. After the study, patients will be grouped as either early stage of the disease (IA-IIA) or advanced stage of the disease (IIB-IVB). The patients crossing over from the early stage of the disease to the advanced stage of the disease group will be analyzed both individually and as a group. Approximately 30% (36/120) of patients are estimated to be in the advanced stage of the disease group. The translational samples in the early stage of the disease group will be compared to samples from the advanced stage of the disease group. The treatments directed against MF are documented throughout this study. Excluded patients will be presented along with the final results. Depending on patient numbers, treatment data will be presented descriptively, or if possible, to support data on treatment predictive biomarkers.

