### Stage of Disease and Modified Severity-Weighted Assessment Tool

Patients will be staged according to the TNMB classification [8]. The extent of disease in the skin will be measured according to the Modified Severity-Weighted Assessment Tool [6,7]. Progression or regression will be defined as a shift from one stage to another.

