## Discussion

### Principal Findings

This study aims to find potential predictive and prognostic biomarkers in patients with MF and SS. This study will investigate translational samples from skin and blood concerning the stage of the disease over time, which has the advantage of monitoring patients with consecutive samplings to be able to capture changes before and during a possible progression. This study will be able to compare differences in patients with early (IA-IIA) and advanced (IIB-IVB) stages of the disease. It will also be possible to analyze the data separately for patients with MF and SS, respectively. The translational samplings in this study are chosen to be able to detect changes in the immune system and in tumor cells, as well as changes in the skin barrier function and the skin microbiota. There is a clinically unmet need to find new predictive and prognostic biomarkers in MF and SS, and studies further exploring these areas are therefore a high priority. The research team, techniques, and management presented in this protocol have capacities to investigate new aspects and bring new knowledge to the field of CTCL. This study combines a multidisciplinary outpatient clinic with extensive translational research sampling, which has considerable potential to lead to true patient benefit.

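### Patients get a single early-or-advanced label after the study with no deciding stage named; if a later stage decides it, group membership depends on progression

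*Protocol article*

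**What the plan says.** The grouping rule is in the Results section of the protocol article: "After the study, patients will be grouped as either early stage of the disease (IA-IIA) or advanced stage of the disease (IIB-IVB". The same paragraph then compares the translational samples of one group with those of the other. The Statistical Analysis section names the methods for this contrast: principal component analysis and the Mann-Whitney U test. For survival it promises Kaplan-Meier plots and mentions no comparison between the two groups.

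Patients who move from early to advanced "will be analyzed both individually and as a group". The article does not say whether they also count in the early or the advanced group. It does not mention patients who move the other way.

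The outcome is built from the same variable. Under the heading on stage of disease: "Progression or regression will be defined as a shift from one stage to another". Stage is reassessed throughout ("The evaluation of the stage of the disease will be observed every 3 months according to the TNMB classification"), and so are the markers ("Sampling of each patient will be performed every 3 months for 3 years").

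On group size: "Approximately 30% (36/120) of patients are estimated to be in the advanced stage of the disease group". Whether this is the number at inclusion or at the end is not stated. Prognosis of MF and SS puts early-to-advanced progression at about 25%, with no time window. Goals of This Study sets the primary objective as markers for 6-month progression-free survival.

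**The concern.** A single label per patient, assigned when follow-up is complete, is applied to samples collected over up to three years. If the label reflects the last or the worst stage, a patient who progresses takes the advanced label, and so do the samples taken while that patient was still in an early stage. If crossers are instead set apart, those samples leave the early group. In both cases the patients who remain early have been selected for not having crossed, which is information from the future relative to the sample.

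This affects most the markers the study is looking for. A marker that truly precedes progression will differ between crossers and non-crossers at baseline. Moving the crossers out of the early group turns that difference into an apparent early-versus-advanced difference. The Principal Findings section presents serial sampling as a way "to be able to capture changes before and during a possible progression"; one label per patient blurs the two periods in the main comparison. The Results section also says that analysis is in progress and accepts early publication of selected findings, so the rule is needed now.

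**Working it through.** **1. The article's own figure.** 36/120 = 0.30, so the stated 30% reproduces. If 36 is the number at inclusion, 120 − 36 = 84 patients start early.

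**2. Possible deciding stages, set against the text.**

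| Deciding rule | Fit with the Results section | Membership depends on outcome? |
|---|---|---|
| Stage at inclusion | Poor: nobody could then cross into the other group | No |
| Stage at sampling | Poor: one patient could hold both labels, against the either/or wording | No, for cross-sectional comparisons |
| Last or worst stage | Fits a label given after the study | Yes |
| Crossers set apart | Fits the separate analysis of crossers | Yes |

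None is named and none is excluded.

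**3. Illustrative number of crossers.** Assume 25% cross over T years at a constant hazard, with T = 5 to 10. Hazard = −ln(0.75)/T, and the 3-year proportion is 1 − 0.75^(3/T).
- T = 5: 1 − 0.75^0.6 = 0.159; 84 × 0.159 = 13.3 patients.
- T = 10: 1 − 0.75^0.3 = 0.083; 84 × 0.083 = 6.9 patients.

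Over a wider assumed 3-year range of 5%, 10%, 15% and 25%, crossers number 4.2, 8.4, 12.6 and 21. If absorbed into the advanced group, they make up 4.2/40.2 = 10%, 8.4/44.4 = 19%, 12.6/48.6 = 26% and 21/57 = 37% of it.

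**4. Size of the distortion in a baseline marker.** Take a marker whose mean is the same in early and advanced patients at inclusion, but which differs by d SD between early patients who will cross (proportion p) and those who will not. With early mean 0, crossers have mean d(1 − p) and non-crossers −dp. With k = 84p crossers, the apparent advanced-minus-early difference is:
- crossers set apart: p·d;
- crossers absorbed into advanced: p·d + d(1 − p)·k/(36 + k).

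For p = 0.10, d = 1: 0.10 SD set apart, and 0.10 + 0.90 × 8.4/44.4 = 0.27 SD absorbed. Both would be 0 under stage at inclusion.

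**5. Effect on the planned test.** Simulated two-sided Mann-Whitney tests at the 5% level (a level assumed here), 2,000 runs per setting, same set-up. No advanced patient moves down, so last and worst stage coincide. Entries are the percentage of runs with p < 0.05.

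| 3-year crossing (assumed) | Crossers differ by | Stage at inclusion | Crossers set apart | Last or worst stage |
|---|---|---|---|---|
| 5% | 0 | 4.4 | 4.8 | 5.2 |
| 5% | 0.5 SD | 5.0 | 5.0 | 6.4 |
| 5% | 1 SD | 4.4 | 4.9 | 10.4 |
| 10% | 0 | 5.2 | 4.8 | 4.8 |
| 10% | 0.5 SD | 5.1 | 5.4 | 10.5 |
| 10% | 1 SD | 4.5 | 7.6 | 24.9 |
| 25% | 0 | 5.1 | 5.0 | 5.3 |
| 25% | 0.5 SD | 4.6 | 7.9 | 28.2 |
| 25% | 1 SD | 4.6 | 20.8 | 77.2 |

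The marker in the non-zero rows really is related to progression. What is false is the conclusion that it differs by stage at entry.

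**6. Survival, only if curves were drawn by the after-study label.** With identical true death rates, follow-up counted from inclusion, and assumed 3-year risks of 5% to 25% for crossing and 5% to 30% for death, crossers versus never-crossers show a death-rate ratio of about 0.45 to 0.50 instead of 1. This is immortal time: a patient must survive to cross.

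**The case against.** The strongest reply is that the article says when the groups are formed, not which stage forms them. Assigning labels at analysis is compatible with stage at inclusion, and the idea of crossing over implies a starting group. The Principal Findings section speaks of stage over time, which suits labelling by sampling date. Crossers are not ignored: they are analysed separately, and the section on digital spatial profiling plans analyses of samples from before and after progression. The article is also condensed, and a full protocol or analysis plan may fix the time point.

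Much of this stands, and it limits the point. A reader might infer that the groups are defined by the outcome, so that every baseline and survival comparison is biased. The documents do not support that. The deciding stage is unnamed, not stated to be the last or worst. A marker unrelated to crossing shows no inflation in the table above. No survival comparison between the groups is stated. Nor do crossers lack a comparator, since each has earlier samples of their own.

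A reader might also count wrongly labelled samples. At 13 visits each and crossing at mid-follow-up, 7 × 6.5 = 45.5 to 13 × 6.5 = 84.5 early-stage samples would carry the advanced label. That holds only if crossers are absorbed into the advanced group; if they are set apart, the count is zero. It also ignores losses, although 2 withdrawals and 2 deaths are already reported with 18 patients enrolled.

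The reply does not remove the point itself. The article does more than leave a detail out: it gives a rule of one either/or label per patient, assigned after follow-up and carried over to the sample comparison. The two harmless readings are the ones that fit its wording least well.

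**Conclusion.** The point holds in a limited form. The grouping rule leaves open which stage decides the label and where crossers in either direction count in the main comparison. Because a stage shift is also progression, two of the four possible rules make membership depend on the outcome. Under them the early group is selected for not having crossed, and early-versus-advanced comparisons of progression-related markers are distorted.

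The size depends on the rule and on unstated quantities. With the illustrative 7 to 13 crossers of 84, absorbing them into the advanced group matters more than setting them apart. At 10% crossing, the false-positive rate is about 11% to 25% when crossers are absorbed, against about 5% to 8% when they are set apart, for crossers differing by 0.5 to 1 SD. Under stage at inclusion it stays at 4.4% to 5.2% in every setting. These figures assume that 36 is the number advanced at inclusion, that nobody moves from advanced to early, and the crossing rates and marker differences shown.

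**What to change.** In the Statistical Analysis and Results sections, replace the after-study grouping with three statements.

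1. For baseline-marker, prognostic and any stage-grouped survival analysis, the group is the TNMB stage at inclusion and does not change.
2. For cross-sectional early-versus-advanced comparisons, each sample is labelled by the stage on its sampling date. Either one sample per patient is used, or a method that allows for repeated samples; a plain Mann-Whitney test on all samples would not.
3. Early-to-advanced crossing is treated as an event or a time-dependent state. Pre-progression samples are compared with samples from patients still in an early stage at the same follow-up time. Formal matching is optional and may not be feasible with few crossers on varied treatments.

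The text should also say how patients who move from advanced to early are handled, and whether the 36 is counted at inclusion or at the end.

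The cost is small: a wording change and slightly more analysis work. No new data are needed, because stage and samples are already planned every three months.

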**Objective:**

This prospective translational study aims to identify prognostic biomarkers in the blood and skin of patients with MF and SS.

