### Treatments for MF and SS

The therapeutic options for MF and SS range from skin-directed therapy (SDT) to systemic treatment, and the selection of appropriate treatment is primarily based on the stage of the disease. There are only a few randomized controlled trials for the treatment of MF and SS, and current recommendations for treatment are mainly based on consensus meetings and international guidelines [4,5,10]. The treatment of the early stages of MF aims at modulating the immune response in the skin through SDT, such as topical corticosteroids and UV light therapy. Local radiation therapy usually has a good effect in all stages. In early stages that are refractory to SDT or in advanced stages, systemic treatment is used, including retinoid derivatives, low-dose methotrexate, and interferon alfa. In patients with lymphoma cells expressing CD30, targeted chemotherapy with brentuximab vedotin can be used. Further, standard chemotherapy such as gemcitabine or doxorubicin can be used; however, this often results in only short remission periods. Extracorporeal photopheresis can be used in erythrodermic stages of MF and SS and mogamulizumab and alemtuzumab can be used in advanced stages of disease. Highly selected patients with advanced stages of disease can be considered for allogeneic stem cell transplantation. Histone deacetylase (HDAC) inhibitors such as vorinostat and romidepsin are approved by the US Food and Drug Administration but are not commonly used in Europe [16,17]. Total skin electron beam therapy can be used in widespread disease in the skin or before allogeneic stem cell transplantation. Treatment response is unpredictable, and there is an unmet clinical need to find reliable predictive markers.

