### Treatment of MF and SS

The treatments will be given according to clinical routine and national and international guidelines for MF and SS and participation in this study will not affect the choice of treatments. Ongoing treatments will be documented.

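### The stated early-versus-advanced tests cannot separate stage-related marker differences from the effects of treatment, which is itself chosen mainly by stage

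*Protocol article*

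**What the plan says.** **Treatment and stage.** The Introduction (Treatments for MF and SS) states that "the selection of appropriate treatment is primarily based on the stage of the disease". For early disease, "The treatment of the early stages of MF aims at modulating the immune response in the skin through SDT". For early disease refractory to skin-directed therapy, or "in advanced stages, systemic treatment is used, including retinoid derivatives, low-dose methotrexate, and interferon alfa".

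**Treatment in the study.** Methods (Treatment of MF and SS): "The treatments will be given according to clinical routine and national and international guidelines for MF and SS", and "Ongoing treatments will be documented". The eligibility criteria in the article set no condition on current or previous treatment.

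**Analysis.** Methods (Statistical Analysis) names an early-versus-advanced comparison by principal component analysis and, for individual samples, the Mann-Whitney U test. Other translational samples are described, and survival is shown in Kaplan-Meier plots. The Results section repeats the stage comparison and adds that, depending on patient numbers, "treatment data will be presented descriptively, or if possible, to support data on treatment predictive biomarkers".

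**Aims.** The abstract's objective is prognostic only: the study "aims to identify prognostic biomarkers in the blood and skin of patients with MF and SS". Goals of This Study lists markers for progression-free survival. Principal Findings is wider: "This study aims to find potential predictive and prognostic biomarkers in patients with MF and SS". The Conclusions of the main text repeat both terms.

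**The concern.** The grouping variable of the main comparison is, on the article's own account, also the main determinant of treatment. The markers are immune read-outs: serum proteins, cytokines, lymphocyte subsets and the skin microenvironment. If treatment shifts any of them, part or all of the early-versus-advanced difference is a treatment effect. The named methods give no way to tell, although the treatment data are being collected.

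A drug effect could therefore be reported as disease biology and carried forward as a candidate biomarker. A second, smaller issue is the word *predictive*. A marker that predicts benefit from a treatment needs a marker-by-treatment contrast. The listed objectives contain none, and in a non-randomised cohort an association seen among treated patients may be purely prognostic.

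**Working it through.** **1. The plan's own figure.** The Results section expects about 30% (36/120) of patients in the advanced group. 0.30 x 120 = 36, which leaves 120 - 36 = 84 early-stage patients. The figure reproduces, and the contrast is 84 versus 36. The article states no alpha, power or effect size, so there is nothing further to reproduce.

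**2. Does the stated analysis separate stage from treatment?**

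| Step | What the article fixes | Consequence |
|---|---|---|
| Treatment choice | Mainly by stage | Treatment shares differ between groups |
| Allocation | Clinical routine, not randomised | The design does not break the link |
| Sampling | Every 3 months for 3 years, under whatever is being given | Markers are measured on treatment |
| Group comparison | PCA and two-group Mann-Whitney | Neither has a place for treatment |
| Use of treatment data | Descriptive, or conditionally in support of predictive markers | No method tied to the stage contrast |

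**3. Size of the mixing (inputs assumed, not in the documents).** Let a treatment shift a marker by *d* SD, with shares p_adv and p_early on it, and let stage have no effect other than through treatment. The expected group difference is then

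(p_adv - p_early) x d.

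- 80% versus 20%, d = 0.8: 0.60 x 0.8 = 0.48 SD
- 60% versus 40%, d = 0.8: 0.20 x 0.8 = 0.16 SD
- 80% versus 20%, d = 0.5: 0.60 x 0.5 = 0.30 SD

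Simulated rejection rates for the unadjusted Mann-Whitney test (84 versus 36, normal marker, two-sided 5%):

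| Treated, advanced v early | Shift d | Rejection rate |
|---|---|---|
| 80% v 20% | 0.8 SD | about 60% (60-62% across repeated simulations) |
| 60% v 40% | 0.8 SD | about 11% (11-12%) |
| 80% v 20% | 0.5 SD | about 30% |
| 80% v 20% | 0.25 SD | about 11% |
| any | 0 | about 5% |

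**4. What adjustment does.** In the same kind of simulation, regression of the marker on stage and treatment returns the rejection rate to about 4-6%. The cost is precision. Unadjusted, the standard error of the stage effect is sqrt(1/84 + 1/36) = 0.20 SD. Adjusted, it is about 0.22 SD at 70% v 30%, 0.24 SD at 80% v 20% and 0.32 SD at 90% v 10%.

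**5. The predictive use.** Assume two evenly used treatments, a marker split in half, a 35% response rate in three cells and 75% in the fourth (a 40-point interaction). The variance sum is 3 x 0.35 x 0.65 + 0.75 x 0.25 = 0.87.

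- 36 advanced patients, 9 per cell: SE = sqrt(0.87/9) = 0.311; 0.40/0.311 - 1.96 = -0.67; power about 25%.
- All 120 patients, 30 per cell: SE = sqrt(0.87/30) = 0.170; 0.40/0.170 - 1.96 = 0.39; power about 65%.

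The article lists many treatments, so two even groups is a favourable assumption.

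**The case against.** Several counter-arguments have force.

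- **The article does not rule out adjustment.** A reader might infer that treatment will never be adjusted for. The text does not say so: it allows a conditional use of treatment data beyond description, and covariate lists are commonly left to a full protocol or SAP that is not shown. This stands. The criticism is confined to the tests the article does name.
- **The immune effect of systemic drugs is not stated in the treatment section.** That section attributes immune modulation to skin-directed therapy, and only in the skin, whereas the primary markers are in blood. A shift in blood markers from systemic drugs is plausible, but it is an assumption here. This stands, and is one reason why the size cannot be fixed.
- **Treatment is partly downstream of stage.** The unadjusted stage difference is a real quantity, and adjusting changes the question. The Results section also reads a stage shift as progression or treatment response, so treatment feeds back on stage. This stands: an adjusted analysis should sit beside the unadjusted one and not replace it.
- **Serial sampling helps.** Samples before and after progression reduce reliance on the between-group contrast. This stands only in part, because treatment may change at the same time and no within-patient treatment model is stated.
- **The predictive aim is hedged.** It is worded as potential and conditional on numbers, and the formal objectives are prognostic. A reader might infer that predictive markers cannot be supported from these data at all. That is too absolute: treatment varies within stage, since systemic therapy is also used in refractory early disease and local radiation in all stages. What holds is that the plan as written names no analysis that would separate prediction from prognosis.

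**Conclusion.** The point holds for the analysis the article names. Treatment selection by stage, routine-care allocation and an unadjusted two-group comparison are all stated, and together they mean that a significant early-versus-advanced difference cannot be attributed to disease rather than treatment. The threat is to interpretation; the stage difference as a description remains valid.

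The existence of the problem needs one assumption beyond the documents: that treatment moves at least some of the measured markers. Its size rests entirely on assumed shares and shifts. The illustrations run from about 11% to about 60% false attribution against a nominal 5%, and nothing in the article places the study within that range. The formal objectives concern progression-free survival, so these figures bear on the stage contrast and not directly on those objectives.

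On the predictive wording, the article's aims are wider than its listed objectives and need to be reconciled.

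**What to change.** 1. Keep the unadjusted early-versus-advanced comparison and label it as descriptive of stage.
2. Beside it, for each marker, add a regression on stage and treatment class at the time of sampling (none, skin-directed, systemic, other), or a rank test stratified by that class, for example van Elteren. PCA and Mann-Whitney take no covariate, so this is an additional analysis and not a changed setting.
3. Add a sensitivity comparison restricted to samples taken off systemic therapy. Attribute a difference to disease biology only if it persists in items 2 and 3.
4. Label any marker-response result within a treatment as an exploratory association, and align the predictive wording in Principal Findings and Conclusions with the prognostic objectives. The term is also part of the study name, so a sentence stating how it is meant would be needed.

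**Cost.** No new data are needed beyond linking the treatments already recorded to each sampling date, and no change in patient management. Precision falls where stage and treatment nearly coincide (illustratively, a standard error of 0.22 to 0.32 SD in place of 0.20 SD). The restricted comparison may select atypical advanced patients, and the resulting claim is more modest. With 18 of 120 patients enrolled by December 2023 but data analysis already in progress, the change is best made before stage comparisons are reported.
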